### Recruitment and Screening

Recruitment and screening will be contracted to Leger that has access to the numbers of household landlines and mobile phones across the country. Recruitment will be conducted using the method of Random Digit Dialing (RDD). Once a potentially eligible participant is identified, the interviewer will confirm the participant’s age, working status, and access to the Internet for personal use, by asking “Do you have access to Internet for personal use, through computer or mobile device?” Then the CIDI-SFMD [16] will be administered. This is to assess MDE in the past 12 months and to ensure the participant is not experiencing a MDE at the time of interview.

If a participant has had MDE in the past 12 months, he will be asked “In the past 2 months or longer, has your mood been much improved or back to normal AND you DIDN’T have any symptom of (key phrases)?” Those who answer “no” will be excluded.

Following this, the sex-specific prediction algorithm for MDE will be administered. The algorithm for men contains 15 questions about personal and family history of MDE, current health status, childhood trauma, and recent negative life events [13]. With the input of the answers to these questions, the algorithm generates the participant’s probability of having MDE in the next 4 years. The original development analysis showed that a probability of 6.51% represented the top 20% of Canadian adult men in terms of the risk of having MDE [13]. In this study, those who have a risk less than 6.51% are considered being at low risk and will be excluded from the study.

### Baseline Assessment

If a person meets the eligibility criteria, the interviewer will administer demographic and occupational characteristics questions, PHQ-9 for depression, GAD-7 for anxiety, perceived risk of having MDE, the HPQ, LEAPS, self-rated physical health, alcohol use, sleep disturbance, anger, quality of life, and mental health service use.

### Online Assessment

To ensure the use of the Internet, participants who complete the baseline telephone assessment will be instructed to complete a short online survey as the last step of the baseline assessment and informed consent. The online survey will include questions about Internet use with the 12-item Job Content Questionnaire [25] used in the Statistics Canada survey to measure self-reported work stress, and consent to participation.

### Randomization

Participants who complete the baseline telephone and online surveys will be randomized into intervention and control groups. The randomization will be conducted and managed by the project coordinator affiliated with the project. To accomplish this, 1200 random numbers (between 0 and 1) will first be generated using Excel (“RAND()”) for 1200 study identification (ID) numbers, ranging from 1 to 1200. The 1200 random numbers will then be sorted in descending order and categorized into 3 equal groups with the ID numbers in the first group (n=400) allocated to the control group, the ID numbers in the second group (n=400) allocated to BroHealth only, and the ID numbers in the third group (n=400) allocated to BroHealth plus job coaching.

The Excel sheet with ID numbers and random numbers will be kept and printed out for randomization. For example, if a participant is the 3rd one to complete the online survey, determined by the date of completion, the project coordinator will search for ID #3 on the Excel sheet. If the random number associated with ID #3 is allocated to the second group, this participant will be assigned to the group that will receive BroHealth only.

The date of randomization will be documented. Any outcomes and/or changes that occur after the randomization will be counted to the groups, regardless of course of the BroHealth and job coaching interventions and if the interventions are used by the participants.

After randomization, the project coordinator will contact the participant by email. For those in the control group, the email will include a link to the men’s mental health page of the Movember Foundation website. For those in the BroHealth only group, the email will include all information to the controls, a link to BroHealth log-in page, and the user name and password, whereas for those in the BroHealth plus job coaching group, the email will include all information to the participants in other groups, and instruction to the coaching appointment booking system in BroHealth.

Afterwards, a package including a thank you letter, the Movember Foundation website link to men’s mental health, and Can $20 incentive as appreciation of their participation will be mailed to the participants.

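### The coordinator who assigns men can read the whole allocation list, and IDs follow completion date with no rule for same-day completers

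*Protocol article*

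**What the plan says.** The Randomization section of the Protocol article sets out a definite procedure.

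- **Who runs it:** "The randomization will be conducted and managed by the project coordinator affiliated with the project".
- **How the list is made:** "1200 random numbers (between 0 and 1) will first be generated using Excel (“RAND()”) for 1200 study identification (ID) numbers". Then "The 1200 random numbers will then be sorted in descending order and categorized into 3 equal groups", which gives 400 IDs to control, 400 to BroHealth only and 400 to BroHealth plus coaching.
- **How the list is held:** "The Excel sheet with ID numbers and random numbers will be kept and printed out for randomization".
- **How a man is tied to a row:** the worked example runs "if a participant is the 3rd one to complete the online survey, determined by the date of completion", and then "the project coordinator will search for ID #3 on the Excel sheet". The arm printed against that ID is the arm he gets.
- **When this happens:** "Participants who complete the baseline telephone and online surveys will be randomized into intervention and control groups". Under Online Assessment, consent is part of the online survey, so it comes before allocation.

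Elsewhere, "Recruitment and screening will be contracted to Leger that has access to the numbers of household landlines and mobile phones across the country"; the same firm does the baseline interviews. Under Data Management, the investigators and the follow-up interviewers have no access to group status, and the coordinator does no follow-up interviews.

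**The concern.** Concealment requires that whoever places a participant in the sequence cannot see what comes next, or else has no say over who is placed there. Here neither condition is met. To look up one ID on the sheet, the coordinator must be able to read the sheet, so the coming arms are visible. The ordering rule stops at the calendar date, so for men who finish on the same day it does not say who is third and who is fourth.

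Foreknowledge combined with discretion over order is the route by which selection bias enters after consent. A preference need not be deliberate: a man who seems keener, or more in need, could be given the row with coaching. Nothing in the article says that the coordinator is kept from baseline information. Because the rule defines no correct order within a day, a departure from it could not be recognised later.

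**Working it through.** **Step 1. The plan's own figures.** The Sample Size Calculation section gives 374 per arm for 0.8% versus 3.9%, power 0.80, alpha .05. The pooled two-proportion formula (two-sided, no continuity correction) returns 374, with power 0.800 at 374 and 0.826 at 400 per arm. The allocation of 3 × 400 = 1200 agrees with the recruitment target. So the design figures are sound, and this point alters none of them.

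**Step 2. What the ordering rule determines.** Set the two statements side by side: the ID is the rank in completion, and rank is fixed by date. A man who is the only completer on his date has a determined ID. If *m* men finish on one date, the rule fixes the set of *m* IDs that they occupy but not which man takes which. If those *m* rows hold more than one arm, the rule does not determine those men's arms.

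**Step 3. How often that would occur.** The recruitment period is not given, so *D* days is an assumption. Take 1200 completions spread evenly at random over *D* calendar days.

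- Share of men with at least one other completer on their date: 1 − (1 − 1/*D*)^1199.
- Share in a same-date group spanning more than one arm: approximately 1 − (1 − 2/(3*D*))^1199, since another row is in a different arm with probability 800/1199 = 0.667. Simulation (200 runs) gave the values in the last column.

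| Assumed period *D* | Completions per day | Share a date | Same-date group spans more than one arm |
|---|---|---|---|
| 180 days | 6.67 | 99.9% | 98.9% |
| 365 days | 3.29 | 96.3% | 88.9% |
| 540 days | 2.22 | 89.2% | 77.3% |
| 730 days | 1.64 | 80.7% | 66.7% |

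For 365 days the first formula is 1 − (364/365)^1199 = 1 − 0.037 = 0.963. If completions cluster on some days rather than spreading evenly, ties become more frequent.

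**Step 4. What a swap does.** Two neighbouring rows differ in arm with probability 800/1199 = 67%, so exchanging two same-day men usually changes both men's arms.

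**The case against.** The strongest reply is that the usual failure of concealment is largely prevented. A contracted firm finds, screens and interviews the men, nothing suggests that its interviewers see the list, and a man is allocated only after consent and a complete baseline. The coordinator therefore cannot easily steer who enters the trial. That stands, and it rules out the broader inference that allocation is unconcealed from everyone involved. It does not settle which consented man receives which visible row. Blinding at follow-up protects outcome assessment, which is a separate matter.

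A second reply is that a condensed article may leave custody of the list and tie-breaking to the full protocol, and that date may be shorthand for a time stamp. If so, the discretion disappears and only the visibility of the list remains. But the article gives a worked example of the rule, and that example uses the date and a sheet that the coordinator searches.

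Three stronger readings are tempting and are not supported:

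- *That the list lies open to the team.* The article says only that it is kept and printed. It is silent on access, and investigators and follow-up interviewers are said not to know group status.
- *That the list cannot be audited because RAND() redraws.* The IDs are fixed values. A redraw after sorting changes the displayed random numbers, not the order of the IDs, so the ID-to-arm list and the printout survive. The sequence cannot be regenerated without a seed, but assignments can be checked against the kept sheet, except for the order within a day.
- *That a few swaps would change the primary result.* Expected events per 400 are 15.6 in control (400 × 0.039) and 3.2 in an intervention arm (400 × 0.008), which looks fragile. But future cases cannot be picked out at baseline. As an illustration with assumed risks, swapping 10 pairs of men at 10% and 4% moves 10 × 0.06 = 0.6 expected events per arm.

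**Conclusion.** The point holds in a limited form. As written, the allocation is not concealed from the person who assigns it, and the ID rule leaves that person to settle the order of same-day completers. If recruitment takes 12 to 24 months with even accrual, this covers about 96% to 81% of men, and about 89% to 67% are in a group where the order can decide the arm. Both ranges rest on the assumed period.

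They measure how often the rule fails to determine the allocation. They do not estimate bias, and the documents give no ground for expecting misuse. The weakness is worth closing before enrolment because it is cheap to remove and the right order within a day cannot be reconstructed from the date alone.

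**What to change.** Amend the Randomization section in two respects.

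1. Set the study ID automatically from the online survey's submission date and time, with a stated rule for exact ties.
2. Replace the readable printed list with a locked, logged file or web tool that releases one allocation at a time, only after the ID is fixed.

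A minor addition: generate the list once with a seeded routine in Stata, the package already named for the analysis, and archive the code and output. The list can then be regenerated as well as audited.

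The cost is a short amendment and a few hours of set-up. The coordinator would request each allocation instead of reading it from a sheet. Sample size, power, visits and the 1:1:1 ratio are unaffected.

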### Follow-Up Assessments

The post-randomization assessments will be conducted at 6 and 12 months. At the 6- and 12-month assessments, information regarding demographic and occupational characteristics questions, including changes in marital status and employment, alcohol use, self-rated physical health, CIDI-SFMD, PHQ-9 for depression, GAD-7 for anxiety, WHO’s HPQ, sleep disturbance, anger, quality of life, and mental health service will be collected.

It is anticipated that time is needed to schedule follow-up interviews and there will be conflicts with scheduled interviews (eg, some participants may have to cancel a scheduled interview, or some do not respond to a scheduled phone call). Therefore, a 2-month interview window will be allowed for each follow-up interview.

To obtain in-depth information about how BroHealth affects men’s behaviors and risk profile, qualitative interviews will be conducted via telephone with 10% of the participants in the intervention groups at the end of the RCT (ie, after the 12-month assessment). The participants will represent those with diverse outcomes (clinical and occupational trajectories, and employment status changes). Qualitative interview data will yield in-depth data about the impacts of receiving BroHealth and job coaching on the outcomes. These data will be used to support and interpret the primary quantitative data base. The multiple forms of evidence generated through mixed methods designs are particularly useful for illuminating complex health issues [26].

### Data Management

The telephone interview firm will transfer password-protected baseline data to the principal investigator (PI) on a weekly basis. The 6- and 12-month follow-up assessments will be conducted at the telephone interview laboratory at the Mathison Centre for Mental Health Research & Education, University of Calgary. One month before the scheduled follow-up interviews, letters will be sent to the participants to remind them of the upcoming interview. An interview log will be developed for each participant to document interview time, schedule, call-back, contact information, and for the interviewer to make comments. All data will be kept confidential and stored on password-protected computers at the telephone interview laboratory and the PI's office, which are under 24/7 security surveillance.

Over the course of the trial, the PI and research staff will examine the data on a regular basis by running cross tabulation, frequency distribution, and estimation of means and proportions to ensure the quality of the data and identify missing values and potential outliers. If missing values and outliers are found, the records will be referred back to the interviewer for clarification or call-back.

After the 12-month interview, participants’ group status will be linked with interview data by study ID numbers. Over the study period, the investigators and the interviewers who conduct the follow-up interviews in Calgary will not have access to participants’ group status. The Leger interviewers, who conduct the baseline assessment and the project coordinator who manage the randomization process, will not be involved in follow-up interviews.

A sub-committee has been formed for this trial. The committee members will communicate via teleconference on a bi-monthly basis to review and discuss the progress, operational issues, final data analysis, and results interpretation.

### Statistical Analysis

All data analyses will be conducted using the most recent version of STATA. An Intention-to-treat (ITT) principle will be used in the analysis (eg, initial intervention assignment rather than intervention received will be used in the analysis).

For the primary objective, the proportions of MDE over 12 months will be estimated for each group and will be compared using chi-square tests between control versus intervention #1, and control versus intervention #2. Logistic regression modeling will be used to examine the effect of the intervention on the outcome, controlling for the effects of baseline confounders. Contrast analysis will be conducted to compare different intervention groups (intervention #1 vs intervention #2) as one of the secondary objectives.

For the secondary objectives, the distributions of the changes in the depression and anxiety scores at 6 and 12 months in the intervention and control groups will be examined. The means of the changes between the intervention and control groups will be compared using *t* tests.

If the assumption of normal distribution is violated, transformation or non-parametric testing will be used. Analysis of variance (ANOVA) will be conducted to examine between group differences (separately for the 6- and 12-month assessments), controlling for the effects of baseline characteristics. Repeated-measures mixed models will be used to examine intervention effect (time x intervention), controlling for the effects of baseline characteristics. The analyses will be repeated for absenteeism and presenteeism (secondary objectives).

An economic evaluation will quantify the costs associated with work productivity loss and absence from work. Self-report measures of work performance on the HPQ can be converted into a percentage of work productivity hours and total hours of work absence. The total combined hours of work performance can then be assigned a dollar value based on consulting industry standard practices for estimating the value of an hour of work absence/productivity, typically a multiplier (eg, 1.5 or 2.0) of the employee hourly compensation rate [27,28]. The hourly compensation rate (wages and benefits combined dollar value) will be estimated for each respondent based on the mid-point of the income category level reported on the baseline assessment. The analysis will then compare the intervention versus control groups for net changes over time to determine if the intervention has a relatively more positive outcome in average work performance over the study period on a per participant basis. This dollarized outcome can then be compared to the cost of providing the intervention to yield an overall cost-benefit or return on investment test [29].

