#### Secondary Outcomes

Secondary outcome variables are changes in depression and anxiety scores, and absenteeism and presenteeism. Depression will be measured by the 9-item Patient Health Questionnaire (PHQ-9); anxiety will be measured by the 7-item Generalized Anxiety Disorder (GAD-7). The PHQ-9 is a widely used scale for assessing depressive symptoms [18], which scores each of the 9 symptoms from 0 (not at all) to 3 (nearly every day) [18]. A PHQ-9 score of greater than or equal to 10 has a sensitivity of 88% and a specificity of 88% for MDE [18]. The GAD-7 is widely used as a general screen for common symptoms of anxiety. The GAD-7 has good reliability and validity. A cut point was identified that optimizes sensitivity (89%) and specificity (82%) [19].

Absenteeism and presenteeism will be measured by the WHO’s Health Performance Questionnaire (HPQ) [20,21] and the Lam Employment Absence and Productivity Scale (LEAPS) [22]. The HPQ is a brief self-report questionnaire that obtains screening information about the prevalence and treatment of commonly occurring health problems, and information about 3 types of workplace consequences (sickness absence, presenteeism, and critical incidents). LEAPS is a validated scale for measuring occupational functioning for workers with depression.

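### Secondary scores: unadjusted change-score t tests and a normality-triggered switch should give way to one lead mixed model adjusted for the baseline score

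*Protocol article*

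**What the plan says.** The Secondary Outcomes section of the protocol article defines the endpoints: "Secondary outcome variables are changes in depression and anxiety scores, and absenteeism and presenteeism". Follow-up is at two visits: "The post-randomization assessments will be conducted at 6 and 12 months".

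The Statistical Analysis section then sets out these steps for the depression and anxiety scores:

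- A test on change from baseline, with no covariates: "The means of the changes between the intervention and control groups will be compared using" t tests.
- A data-dependent switch: "If the assumption of normal distribution is violated, transformation or non-parametric testing will be used". It gives no criterion for a violation and does not choose between the two alternatives.
- An ANOVA that "will be conducted to examine between group differences (separately for the 6- and 12-month assessments), controlling for the effects of baseline characteristics".
- A longitudinal model: "Repeated-measures mixed models will be used to examine intervention effect (time x intervention), controlling for the effects of baseline characteristics".

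The same set is repeated for absenteeism and presenteeism. The section does not order the methods, name a lead visit, or say whether the baseline characteristics include the baseline value of the score being analysed. The Baseline Assessment section does schedule the PHQ-9, GAD-7, HPQ and LEAPS before randomization, so those baseline scores will be available.

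**The concern.** Three features of the written plan weaken it.

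**Precision.** The first-listed test subtracts the baseline score instead of regressing on it. Under randomization both approaches target the same mean difference between arms, so bias is not the issue. Subtraction fixes the baseline coefficient at 1, which in general is not the value that minimises the variance.

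**The switch.** Comparing means does not need normally distributed scores at about 400 per arm. The alternatives also answer other questions: a rank test on changes no longer compares means, and a transformed analysis compares means on another scale. The estimand would then depend on how the data happen to look.

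**No lead result.** Each score yields results from several methods at two visits. If they disagree, the text gives no basis for saying which one stands. A favourable result could then be put forward afterwards, even with no intention to select.

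**Working it through.** **The plan's own figure.** The only sample-size figure is 374 per arm for the primary outcome (0.8% v 3.9%, power 0.80, alpha 0.05). It reproduces:

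n = [1.96·√(2 × 0.0235 × 0.9765) + 0.8416·√(0.008 × 0.992 + 0.039 × 0.961)]² / 0.031² = (0.4199 + 0.1794)² / 0.000961 ≈ 374.

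The document states no power or precision for the secondary scores, so this point does not depend on that figure.

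**Inputs.** The planned number is 400 per arm (Sample Size Calculation). The document gives neither the baseline-to-follow-up correlation r nor k = baseline SD / follow-up SD. Both are assumptions here, shown over a range.

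**Formulas.** In units of the follow-up variance, per participant:

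- change score: 1 + k² − 2rk
- baseline-adjusted: 1 − r²

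The first minus the second is (k − r)², which is never negative. In large samples the change-score test can therefore match the adjusted analysis (when k = r) but cannot beat it. With k = 1 the ratio is (1 − r²) / [2(1 − r)] = (1 + r)/2.

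**Variance of the adjusted estimate relative to the change-score t test:**

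| r | k = 1 | k = 0.8 |
|---|---|---|
| 0.3 | 0.91/1.40 = 0.65 | 0.91/1.16 = 0.78 |
| 0.5 | 0.75/1.00 = 0.75 | 0.75/0.84 = 0.89 |
| 0.7 | 0.51/0.60 = 0.85 | 0.51/0.52 = 0.98 |

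At r = 0.5 the cut in variance is 25% for k = 1, about 11% for k = 0.8, and about 5% for k = 0.7 (0.75/0.79 = 0.95). It would exceed 25% if k were above 1.

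**In detectable differences.** With 400 per arm, 80% power, two-sided 5%, r = 0.5 and k = 1:

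- change score: 2.80 × √(2 × 1.00/400) = 0.198 SD
- adjusted: 2.80 × √(2 × 0.75/400) = 0.172 SD

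**Is the switch needed?** A null simulation used 3,000 runs per setting, 400 per arm, two arms, complete data and r = 0.3, 0.5 and 0.7. With log-normal scores the t test on change rejected in 4.9% to 5.3% of runs, and the baseline-adjusted model in 4.9% to 5.6%. Skew of that degree does not call for a switch. The simulation did not include hours with many zeros.

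**What an open choice can do.** These figures come from the same simulation, with normal and log-normal scores, one score and one arm comparison:

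- one named adjusted model at 12 months: 4.9% to 5.8% false positives
- smallest p of the t, rank and adjusted tests at 12 months: 7.8% to 9.9%
- the same three tests at both visits: 13.9% to 17.1%

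The last two are worst cases. They assume that the smallest p is always the one reported and that the rank test is always available.

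**The case against.** The best defence is that this is a condensed article. Ranking secondary analyses, naming covariates and writing out the model are commonly left to a statistical analysis plan, which is not shown. Adjusted ANOVA and a mixed model are already listed, so the proposal promotes a planned method and adds no new one. Part of this stands: the absence of a lead analysis would be weak as a finding on its own. But the article does commit itself to an unadjusted test on change and to a data-driven switch. A later plan would have to demote the first and drop the second.

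Several stronger readings are tempting and are not supported:

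- **A secured 25% gain, like a third more participants.** This needs r = 0.5 and equal SDs, and the document gives neither. Men in a current episode are excluded at entry, so a narrower baseline spread is plausible, though not shown.
- **A gain over everything planned.** It is a gain over the t test. With complete data there is little gain over the planned ANOVA if that includes the baseline score.
- **An interaction test that misses a constant effect.** That follows only if baseline is not one of the modelled time points. With baseline as a time point, time x intervention is the usual test of effect, and the text does not say which is meant.
- **A log transform applied to negative changes.** The text names neither the transformation nor the variable to be transformed.
- **Harm to the return-on-investment analysis.** The economic evaluation is described separately and does not run through these tests.
- **Participants lost altogether.** A per-visit test loses a man only at the visit he missed.

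**Conclusion.** The point holds in limited form. The plan puts first a test that is never more precise than baseline adjustment, attaches a switch that is unnecessary and changes the estimand, and leaves three kinds of analysis without an order.

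The size is uncertain. The variance saving over the t test is 15% to 35% for assumed r of 0.7 down to 0.3 with equal SDs. With a baseline SD 0.8 of the follow-up SD it is 2% to 22%, and about 11% at r = 0.5. The false-positive figures are upper illustrations under assumed correlations, not a forecast of how the team will report.

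The primary outcome and its sample size are untouched. A reader might infer that one model would remove all choice of result. It would not: several outcomes and three arm comparisons remain, and the comparison of the two intervention arms is a stated objective in its own right.

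**What to change.** For each continuous secondary outcome measured at follow-up, name the mixed model already listed as the lead analysis:

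- **Outcomes:** the 6- and 12-month scores.
- **Terms:** arm, visit, arm-by-visit, baseline score, and baseline-score-by-visit.
- **Lead estimate:** the arm contrast at 12 months, not the time x intervention term. With baseline as a covariate, that term tests only whether the effect differs between the two visits. The 6-month contrast is supportive.
- **Skewed hours:** robust or bootstrap standard errors.

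Delete the normality-triggered switch, and label the t tests and per-visit ANOVA as supportive.

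The cost is a change of wording and slightly more modelling work. For the PHQ-9, GAD-7 and HPQ no extra data are needed, since each is scheduled at baseline and at both follow-ups. LEAPS is named as an absenteeism and presenteeism measure and is scheduled at baseline, but the Follow-Up Assessments section does not list it. The model can cover LEAPS only if it is also collected at follow-up. How to handle multiplicity across outcomes and arm comparisons needs a separate statement. The change should be made before group status is linked to the interview data, which the Data Management section places after the 12-month interview.
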